## Abstract

**Background:**

Nonspecific neck pain (NNP) is a highly prevalent musculoskeletal condition worldwide, yet optimal noninvasive treatments remain to be established. Tuina and extracorporeal shock wave therapy (ESWT) are both commonly used in clinical practice, but comparative evidence is limited.

**Objective:**

This study aims to compare the clinical efficacy of Tuina versus ESWT in patients with NNP.

**Methods:**

In this randomized, controlled, single-blind trial, 58 patients with NNP will be allocated in a 1:1 ratio into 2 groups: Tuina therapy and ESWT. The Tuina group will receive 30-minute sessions 3 times per week for 4 weeks (12 sessions total). The ESWT group will receive interventions on days 1, 5, 10, 15, 20, 25, and 30 (7 sessions total). The primary outcome measure will be pain intensity measured by the visual analog scale. Secondary outcome measures will include the Neck Disability Index, cervical active range of motion, shear wave elastography (SWE) using musculoskeletal ultrasound, and serum inflammatory factors. All outcome measures will be assessed at baseline, during treatment (2 and 4 wk), and at the 8-week follow-up, except for SWE and inflammatory factors. SWE will be measured at baseline, 4 weeks, and 8-week follow-up; inflammatory factors will be measured at baseline and 4 weeks.

**Results:**

Recruitment began on January 4, 2026, and is expected to be completed by August 2026. As of March 30, 2026, of the planned 58 participants, 26 had been enrolled. Data collection, including follow-up, is projected to finish by October 2026. Data analysis will commence after data collection is completed, and the results are anticipated to be submitted for publication in early 2027.

**Conclusions:**

This trial will provide direct comparative evidence to determine whether Tuina is superior to ESWT for reducing pain and disability in NNP, thereby informing evidence-based clinical decisions. Key design limitations include the inability to blind participants, which we mitigated by using blinded outcome assessors and rigorous allocation concealment.

## Introduction

Neck pain is defined as an unpleasant sensory and emotional experience associated with actual or potential tissue damage, located in the anatomical region extending from the superior nuchal line to the level of the scapular spine [1]. It ranks among the top 5 chronic conditions for prevalence and years lived with disability and represents a substantial individual and socioeconomic burden. Global estimates for 2019 recorded 222.7 million prevalent cases and 22.1 million years lived with disability [2-5]. It is most common in middle age, and women are more affected than men [6].

Most neck pain cannot be attributed to a specific pathoanatomical cause and is therefore classified as nonspecific neck pain (NNP) [7,8]. When pain persists for at least 3 months in the absence of systemic disease, it is termed chronic NNP, which is typically driven by postural and mechanical factors [9,10]. The 1-year incidence of NNP is estimated at 30% to 50%, and approximately 20% of cases become chronic, mainly affecting young adults; consequently, early diagnosis and intervention are critical [11].

A wide range of pharmacologic and nonpharmacological interventions has been recommended for neck pain; however, systematic reviews report only modest or inconsistent benefits, and concerns about adverse effects limit the use of medications such as nonsteroidal anti-inflammatory drugs [10,12-15]. Based on our preliminary literature review and visualization analysis, manual therapy was identified as one of the top 10 keywords, as shown in Figure 1.

**Figure 1. F1:**
[figure not shown]
Keywords co-occurrence network of published studies on nonspecific neck pain, visualizing thematic clusters in the research field.

Research shows that Tuina therapy combined with Yijinjing exercise in patients with NNP has a certain clinical effect on pain, functional recovery, and anxiety [16]. For patients with chronic neck pain, it is effective, safe, and relatively economical to perform Tuina therapy 6 times within 3 weeks [17]. Separately, extracorporeal shock wave therapy (ESWT) has been used to deactivate myofascial trigger points in the upper trapezius of individuals with NNP, with promising results [18]. However, these 2 modalities have never been directly compared in a randomized trial. Moreover, existing studies are limited by small sample sizes, the absence of blinding, and short follow-up, leaving the comparative effectiveness and the underlying mechanisms—such as effects on muscle elasticity and systemic inflammation—largely unexplored.

We therefore hypothesized that Tuina therapy would be superior to ESWT in reducing pain intensity and neck-related disability and that both interventions would improve cervical range of motion and muscle elasticity and downregulate serum inflammatory biomarkers. To test this hypothesis, this randomized controlled trial aimed to evaluate the superiority of Tuina therapy over ESWT for NNP. The specific objectives are (1) to compare the 2 interventions in terms of improvements in pain, disability, cervical range of motion, and muscle elasticity and (2) to evaluate their effects on chronic inflammation by measuring the expression of relevant factors in patients’ serum before and after the intervention.

## Methods

### Ethical Considerations

All trial procedures involved in this study were approved by the medical research ethics review committee of the General Hospital of Ningxia Medical University (approval number KYLL-2025-0083, Yinchuan, China, date: January 24, 2025) and prospectively registered at the International Traditional Medicine Clinical Trial Registration platform (registration number ITMCTR2025001377) [19]. The trial will follow the CONSORT (Consolidated Standards of Reporting Trials) guidelines and fulfill the requirements of the SPIRIT (Standard Protocol Items: Recommendations for Interventional Trials) checklist (Checklist 1). All interested participants will be required to sign the written informed consent form with a clear understanding of the study before participation and clearly understand all the contents and processes of the study.

### Study Design

This is a single-center, randomized, controlled, parallel-group, assessor- and analyst-blinded, superiority trial comparing Tuina therapy versus ESWT in patients with NNP. The trial will be conducted at the General Hospital of Ningxia Medical University. Eligible participants will be randomly assigned in a 1:1 ratio to either the Tuina group or the ESWT group. Both groups will receive their respective intervention in addition to standardized exercise therapy over a 4-week treatment period, followed by a 4-week follow-up (total study duration: 8 wk). The flowchart of the trial process is shown in Figure 2, and the trial period is shown in Figure 3.

**Figure 2. F2:**
[figure not shown]
Study flowchart. CONSORT (Consolidated Standards of Reporting Trials) diagram showing participant enrollment, randomization, interventions, and follow-up in a randomized controlled trial of Tuina versus extracorporeal shock wave therapy for nonspecific neck pain. NDI: Neck Disability Index; VAS: visual analog scale.

**Figure 3. F3:**
[figure not shown]
Schedule of enrollment, interventions, and assessments (SPIRIT [Standard Protocol Items: Recommendations for Interventional Trials] schedule) in a randomized controlled trial of Tuina versus extracorporeal shock wave therapy for nonspecific neck pain. AROM: active range of motion; NDI: Neck Disability Index; SWE: shear wave elastography; VAS: visual analog scale.

Any important protocol modifications will be submitted to the Medical Ethics Committee for approval prior to implementation. Amendments will be updated in the clinical trial registry and communicated to all study personnel through meetings or written notifications. If modifications affect the rights, safety, or willingness of participants to continue, the informed consent form will be updated and participants will be reconsented.

### Recruitment Procedure and Eligibility Criteria

All participants will be recruited through hospital social network media (WeChat) information, hospital posters, and the outpatient department of rehabilitation medicine. According to the diagnostic criteria, inclusion criteria, and exclusion criteria, patients with NNP were screened out.

### Diagnostic Criteria

Diagnosis of NNP was based on the 2014 Canadian evidence-based guidelines for chiropractic therapy in the treatment of adult neck pain and the consensus plan for clinical diagnosis and treatment of NNP through muscle massage (2024 edition) [20,21]: (1) pain located in the anatomical region of the cervical spine; (2) no specific cause such as trauma, infection, tumor, or neuropathy; (3) may or may not be accompanied by headache, restricted cervical motion, or stiffness in one or more directions.

### Inclusion Criteria

Participants will be eligible if they meet all of the following criteria: (1) meet the above diagnostic criteria; (2) age 18 to 60 years old, gender unlimited; (3) 3 points ≤ visual analog scale (VAS) ≤ 5 points; (4) pain duration for more than 3 weeks (ie, beyond the acute phase as defined by the DEGAM S3 [German Society of General Practice and Family Medicine] guideline), which classifies acute neck pain as 0 to 3 weeks [22]; and (5) voluntary participation with signed informed consent.

### Exclusion Criteria

Participants will be excluded if they have any of the following conditions: (1) history of neck trauma, surgery, or tumor; (2) severe cardiac, cerebral, renal, hepatic, or other major organ diseases, mental or behavioral disorders, or inability to cooperate; (3) receipt of Tuina, ESWT, opioid analgesics, antispasmodic analgesics, or anti-inflammatory analgesics within 3 months before enrollment; (4) a confirmed history of infection or familial genetic disease; and (5) pregnant or breastfeeding women.

### Withdrawal Criteria

Participants will be withdrawn if they (1) have incomplete treatment or missing data, (2) experience serious adverse events (SAEs) that prevent further intervention, and (3) show worsening of the condition or are diagnosed with another serious illness during the study period.

### Randomization and Allocation Concealment

A computer-generated random allocation sequence will be prepared by an independent statistician using IBM SPSS 26.0. We will use randomly permuted blocks of varying sizes (2, 4, and 6) to ensure balance between the 2 groups over time and to reduce predictability. A total of 58 subjects will be randomized in a 1:1 ratio to the Tuina group or the ESWT group.

Allocation concealment will be achieved using sequentially numbered, opaque, sealed envelopes. The envelopes will be prepared by an independent statistician who generates the sequence and will be stored in a locked cabinet accessible only to a designated research coordinator who is not involved in participant recruitment, intervention delivery, or outcome assessment. After a participant completes the baseline assessment and signs informed consent, the next sequentially numbered envelope will be opened by the coordinator to reveal the group assignment. The use of envelopes with identical appearances and sequential numbering prevents any foreknowledge of upcoming allocations. Owing to the nature of the interventions, it is not feasible to blind participants or the therapists delivering Tuina and ESWT. This unavoidably introduces the potential for performance bias and expectation bias in self-reported outcomes. To mitigate these risks, we will implement the following measures:

Blinded outcome assessment: All outcome assessors are blinded to group allocation and are not involved in treatment delivery or data analysis. They will be trained to collect outcomes in a standardized manner and instructed not to discuss treatment with participants.Blinded data analysis: Statisticians and data analysts will work with coded data (groups labeled only as “1” and “2”) and will remain blinded until the database is locked and the primary analysis is completed.Minimizing differential expectations: Participants in both groups will receive a structured information sheet emphasizing that both interventions are evidence-based and that neither is known to be superior to the other, in order to promote equal treatment credibility.Assessment of blinding integrity: At the end of the follow-up period, participants and outcome assessors will be asked to guess group allocation. The proportion of correct guesses will be compared against chance to evaluate the success of blinding procedures for assessors and the effectiveness of expectation management for participants.

After the trial, data will be entered into the database according to subject codes, and the database will be locked after verification. Unblinding will be performed by the project administrator only after all data analyses are completed, at which point the group codes will be revealed.

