#### Primary Outcome Measurement

The VAS is a commonly used instrument for pain assessment, designed to enable patients to quantify their pain intensity using a simple linear scale. A 10-centimeter scale will be employed, with end points labeled “0” (no pain) and “10” (the most severe pain imaginable). Patients will indicate the point on the scale that reflects their current pain experience. The primary efficacy end point is the change in VAS score from baseline to the end of the 4-week treatment period. The VAS is primarily utilized to evaluate pain intensity; it may also serve to compare treatment outcomes and to monitor changes in emotional and functional status.

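### Unblinded participants' allocation guesses, tested against chance, cannot evaluate expectation management

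*Protocol article*

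**What the plan says.** All of the following is in the protocol article.

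- **Blinding status.** Randomization and Allocation Concealment states that "it is not feasible to blind participants or the therapists delivering Tuina and ESWT", and draws the consequence: "This unavoidably introduces the potential for performance bias and expectation bias in self-reported outcomes".
- **Measure aimed at expectation.** The same section offers one: "Participants in both groups will receive a structured information sheet emphasizing that both interventions are evidence-based". The sheet also says that neither treatment is known to be better, so that both should seem equally credible.
- **Check.** "At the end of the follow-up period, participants and outcome assessors will be asked to guess group allocation". The share of correct guesses is then compared with chance "to evaluate the success of blinding procedures for assessors and the effectiveness of expectation management for participants".
- **Use made of the check.** The limitations paragraph of the Discussion lists the analysis of blinding integrity, with blinded assessment and the standardized information, as mitigation of performance and expectation bias. The Abstract's Conclusions describe the inability to blind participants as something "which we mitigated by using blinded outcome assessors and rigorous allocation concealment".
- **Primary outcome.** Under Primary Outcome Measurement the VAS is self-reported: "Patients will indicate the point on the scale that reflects their current pain experience".

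**The concern.** Comparing guesses with chance makes sense for people who are meant not to know the allocation. That is true of the assessors. It is not true of the participants, by the protocol's own statement. For them the plan measures one quantity (knowledge of the treatment received) and interprets it as another (equality of expectation between arms).

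At stake is the only check the article describes on differential expectation, a bias that it says can affect self-reported outcomes, and the primary VAS is one of these. An uninformative check would be reported as an evaluation, and its near-certain result points the wrong way.

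**Working it through.** **1. Number of guesses.** Sample Size Calculation gives 24 per group and 15% dropout: 24 / (1 − 0.15) = 28.2, rounded up to 29 per group, 58 in total. This agrees with the plan. The range is therefore 58 guesses if everyone answers and 48 if only the planned evaluable number does. Under 1:1 allocation, chance is 50%. The plan states no expected number of correct guesses, so there is no figure of its own to reproduce here.

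**2. Rejection boundary.** Let X be the number of correct guesses, X ~ Binomial(n, 0.5) under chance. An exact two-sided 5% test rejects upwards at the smallest r with P(X ≥ r) ≤ 0.025.

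| n | P(X ≥ r − 1) | P(X ≥ r) | r | r / n |
|---|---|---|---|---|
| 58 | 0.043 | 0.024 | 37 | 63.8% |
| 48 | 0.030 | 0.015 | 32 | 66.7% |

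**3. Probability of rejecting.** The true share of correct answers is not in the documents. One arm has 12 manual sessions and the other 7 device sessions, and the participant cosigns a treatment log after each session (Interventions). I assume 90% to 100% correct. At 90% the probability of reaching the boundary exceeds 0.9999 for both n = 58 and n = 48. If all are correct, the two-sided p-value is 2 × 0.5^n, about 7 × 10⁻¹⁸ for n = 58 and 7 × 10⁻¹⁵ for n = 48. Testing each arm separately changes nothing: 2 × 0.5^29 ≈ 4 × 10⁻⁹.

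**4. What the result says about expectation.** Take two cases.

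| Case | Participant knows the treatment | Test against 50% |
|---|---|---|
| Both arms expect equal benefit (sheet worked) | yes | rejects |
| One arm expects much more benefit (sheet failed) | yes | rejects |

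The test gives the same answer in both cases, so it cannot tell them apart. If agreement with chance is taken as success, as it is for assessors, the first case would be reported as a failure of expectation management although the sheet did its work.

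**5. The stated mitigations.** Allocation concealment protects against selection at enrolment. Assessor blinding limits what an assessor can add when the score is collected. Neither acts on the participant's own expectation when marking the VAS. The information sheet might, but the guess does not test whether it does.

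**The case against.** The strongest reply is that little depends on this item. The guess enters no estimate, test, analysis population or decision. The primary repeated-measures model and the sample size are the same with or without it, and the article discloses more than once that participants are unblinded. That is right. It limits the consequence, but it does not make the stated use of the guess valid. Nor can the point be left to a fuller analysis plan: the article itself fixes the question, the time, the comparator and the interpretation.

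A reader might infer more than the documents support:

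- **That the primary VAS difference is biased by a known amount.** The documents contain no figure for the effect of expectation on the VAS. Any size would rest on assumed slopes and imbalances, and would describe unblinded trials in general. Correcting the guess would not reduce it.
- **That the assessor-blinding claim is false and should be deleted.** The article makes no claim specific to the VAS. Assessors are trained to collect outcomes in a uniform way and told not to discuss treatment, which plausibly limits their influence on self-report, and they are also blinded for measured outcomes such as range of motion. The mitigation is partial, and the wording should say so.
- **That the assessor guess comes too late.** Assessments run to week 8. A guess at the end covers unblinding up to then and does not invite assessors to speculate before their last assessment. Week 4 would be closer to the primary endpoint but loses those advantages. This is a trade-off, not an error.
- **That adjusting for an expectation rating taken before allocation would solve the problem.** Randomization balances such a rating on average. As a main-effect covariate it cannot remove or reveal an arm difference created by learning the allocation.
- **That expectation is the trial's main bias.** The article names performance and expectation bias together, without ranking them.

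**Conclusion.** The participant half of the guessing exercise is wrong as written. It is given a purpose, evaluating expectation management, that it cannot serve. Rejection of chance is practically certain (37 of 58 correct suffices) whatever the participants expect, and the natural reading of that result would wrongly count against the information sheet. The one assumption is that at least about 90% of participants can name their treatment, which is hard to doubt for hands-on therapy against a device. The assessor half is sound.

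The defect lies in the evaluation and reporting of a bias. It does not invalidate the primary analysis, and no size of bias in the VAS follows from it.

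**What to change.** 1. Drop the participant guess. Keep the assessor guess as the check on blinding.
2. For participants still to be enrolled, record a short 0-10 rating of credibility or expected benefit for the assigned treatment, once allocation is known and early in treatment, for example after the first session. Report the between-arm difference with a 95% CI as the check on differential expectation.
3. In Randomization and Allocation Concealment and in the Discussion's limitations paragraph, limit the blinding-integrity analysis to assessors.
4. In the Abstract's Conclusions and the same limitations paragraph, state that assessor blinding and allocation concealment do not remove participant expectation from the self-reported VAS.

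**Cost.** An amendment and one or two short questions per participant. Those already past that time point have no rating. With 26 of 58 enrolled by March 30, 2026, at most 58 − 26 = 32 later participants (about 16 per arm) could supply it, plus any of the 26 not yet past their first session, and fewer as recruitment goes on. The estimate will be imprecise: with 16 per arm the 95% CI half-width is 2.042 × SD × √(2/16) = 0.72 × SD, or 1.1 to 1.8 points for an assumed rating SD of 1.5 to 2.5. It should therefore be reported as an estimate with its interval and not as proof of equal expectation. The primary analysis and the sample size stay as they are.

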### Interventions

All interventions will be delivered over a 4-week treatment period, with follow-up assessments conducted 4 weeks after treatment completion. Both groups will receive the same standardized exercise therapy and self-stretching relaxation program. The Tuina group will additionally receive 3-step Tuina therapy, and the ESWT group will additionally receive ESWT. All procedures take place in the treatment room of the Department of Rehabilitation Medicine, General Hospital of Ningxia Medical University. In order to improve the compliance of the subjects, the subjects will receive treatment and related assessment and examination free of charge.

Participants will receive enrollment education on the importance of treatment compliance, appointment reminders 24 hours before each session, flexible scheduling with transportation subsidies, and a treatment log cosigned by the participant and practitioner after each session. Adherence will be monitored through (1) treatment logs cosigned by participant and practitioner after each session, (2) attendance recorded in case report forms, (3) home exercise logs reviewed weekly, and (4) appointment reminders sent 24 hours before each session. Nonadherence thresholds are predefined: participants missing more than 20% of scheduled sessions (ie, ≥3 Tuina sessions or ≥2 ESWT sessions) or completing less than 70% of the prescribed home exercise program will be classified as nonadherent. A per-protocol analysis will be conducted in addition to the intention-to-treat (ITT) analysis. Treatment parameters in the ESWT group will be randomly audited every 2 weeks to ensure protocol consistency.

All interventions will be performed by qualified practitioners. Tuina manipulations will be delivered by practitioners holding a Physician Qualification Certificate and a Physician Practice License in Traditional Chinese Medicine, Acupuncture-Tuina, or Rehabilitation Medicine, with at least 3 years of clinical experience in Tuina. ESWT will be administered by practitioners holding a Physician Qualification Certificate and a Physician Practice License or a nationally recognized rehabilitation therapist certificate, who have completed specialized shock wave training and possess at least 1 year of clinical experience in shock wave therapy. Prior to study initiation, all intervention providers will undergo standardized training on the study protocol and pass a competency assessment. Ongoing quality monitoring will be conducted quarterly throughout the study.

Patients can choose to withdraw from the study at any time. Any significant improvement or deterioration in the condition of a participant, including adverse events (AEs), will be monitored throughout the trial. AEs will be reported to the principal investigator (PI), who will monitor the affected participants and investigate the potential causes.

